## **Outcome Measures**

### *Demographics*

Demographic variables and potential covariates will be recorded at baseline and include:

- Age
- Gender
- Years of education
- Age first tried cannabis
- Age of onset of regular cannabis use
- History of physical and mental ill health
- Family history of cannabis use

### *Clinical*

The Mini International Neuropsychiatric Interview 7.0.2 is a semi-structured diagnostic interview for DSM-V and will be administered by a trained member of the research team. It will be used to screen for current and past mental illness to assess comorbidity. During the telephone screen phase, the MINI screen will be administered to identify those who meet inclusion/exclusion criteria.

### *Questionnaires/Interviews*

#### Screening

- Physical Activity Readiness Questionnaire (9-item)

#### Cannabis Use

- Timeline Follow Back Procedure (3-months)
- Severity of Dependence Scale (5-item)
- Marijuana Withdrawal Checklist – Short Version (15-item)
- Penn Craving Scale (5-item)

#### Other Drug Use

- Alcohol Use Disorders Identification Test – Self Report (10-item)
- Fagerstrom Test for Nicotine Dependence (6-item)

#### Psychopathology (depressive symptoms, psychotic symptoms, anxiety)

- Quick Inventory of Depressive Symptomology (16-item)
- State Trait Anxiety Inventory (20-item)

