### **Secondary hypotheses (outcomes at 3- and 9-months relative to baseline):**

- 2a. Cannabis users in the EXE+ will have reduced cannabis use (freq. of use, % of abstinence days) and psychopathology (depressive and psychotic symptoms), as well as improved cognition (learning, memory) and general well-being (social and occupational functioning).
- 2b. Any improvements in Hypothesis 2a will be mediated by changes in hippocampal integrity.

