### *Inclusion criteria:*

1. Aged 20-55 years
2. Voluntary and able to provide informed consent
3. Fluent in English
4. Current moderate – severe cannabis use disorder

5. Major history of cannabis use (i.e.  $\geq 3$  days per week on average for  $\geq 4$  of the past 6 years)

*Exclusion criteria:*

1. Current engagement in CUD treatment;
2. Presence of a neurological disorder or serious head injury;
3. Lifetime history of bipolar disorder, obsessive-compulsive disorder, post-traumatic stress disorder, psychosis or autism spectrum disorder;
4. Current, unstable use of psychotropic medication;
5. Contraindications for MRI (i.e., metal implants and claustrophobia);
6. Current unstable, or chronic medical illness (i.e., cardiovascular disease, chronic pain, musculoskeletal injury), that would preclude safe engagement in CPET and/or regular physical exercise;
7. Engaging in shift work in the previous six months;
8. Engaging in five or more HIIT sessions within the previous six months;
9. Moderate and/or severe substance use disorder other than CUD;
10. Pregnancy or lactation.
11. Other psychoactive medications or psychosocial treatments will be considered on a case-by-case basis. Where a current psychoactive medication is deemed acceptable, both dose and type must have been stable for a minimum of four weeks prior to baseline assessment, and remain stable throughout the 12-week exercise phase of the study.

Please note, only individuals who are voluntary, able to provide full informed consent and able to adhere to the study procedures will be recruited.

These criteria have been designed to exclude individuals for whom the protocol may pose a risk to physical safety (e.g. history of cardiovascular or musculoskeletal injury, contraindication to MRI) and control for variables which would confound the study results (e.g. neurological abnormalities on brain imaging, pre-existing cognitive impairment on cognitive testing).

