### *Weekly Qualtrics Questionnaire via Smart Phone*

Participants will be sent the Qualtrics link to their email and will be asked to complete the survey within 24 hours.

- Timeline Follow Back Procedure to measure weekly cannabis use
- Adverse Events
- Patient Health Questionnaire (9-item)
- State Anxiety Inventory – Short Form (6-item)
- Warwick Edinburgh Mental Wellbeing Scale – Short Form (7-item)
- Severity of Dependence Scale (5-item)
- Marijuana Withdrawal Checklist – Short Version (15-item)
- Penn Craving Scale (5-item)
- Visual Analogue Mood Scale: 100-point sliding scale indicating how the intensity of the following feelings over the last week:
  - Mood: happy – sad
  - Satisfaction: content – discontent
  - Cannabis craving: no craving – high craving, never – always
  - Energy: energized – lethargic

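### Psychotic symptoms are a named part of Hypothesis 2a, but no listed instrument scores them at baseline and follow-up, so that component cannot be tested as change from baseline

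*Protocol*

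**What the plan says.** The protocol section headed "Secondary hypotheses (outcomes at 3- and 9-months relative to baseline" states under 2a that HIIT participants will show reduced "psychopathology (depressive and psychotic symptoms), as well as improved cognition". Hypothesis 2b adds that improvements in the 2a outcomes will be mediated by changes in hippocampal integrity.

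Under Outcome Measures, Questionnaires/Interviews, the relevant heading is "Psychopathology (depressive symptoms, psychotic symptoms, anxiety". Two entries follow: "Quick Inventory of Depressive Symptomology (16-item" and "State Trait Anxiety Inventory (20-item".

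The Clinical subsection of Outcome Measures describes the Mini International Neuropsychiatric Interview 7.0.2. Its stated purpose is to screen for present and past mental illness and assess comorbidity, with a telephone version used to check eligibility.

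The section Statistical analysis plan says that Hypothesis 2 is tested with linear mixed models comparing change from baseline between the arms, and Hypothesis 2b with longitudinal mediation models.

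**The concern.** A hypothesis about change in a symptom needs that symptom to be scored before treatment and again afterwards. Here the hypothesis and the questionnaire heading both promise psychotic symptoms, while the instruments beneath the heading stop at depression and anxiety. If nothing elsewhere fills the gap, the trial will end with a pre-specified secondary component on which it holds no data. A statistical analysis plan could not repair this: it can define how a score is analysed, but it cannot supply a score that the assessment schedule never collects. A baseline value that was not taken also cannot be recovered later.

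The component has a place in the trial's reasoning. The Background, and the section on the first pilot study, name psychotic symptoms among the harms linked to cannabis use and its hippocampal effects.

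**Working it through.** No figure in the protocol bears on this point, so the check compares the outcomes named with the instruments listed.

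**Step 1. What is needed.** The analysis compares change from baseline between the arms. Each outcome therefore needs a score at baseline and at one or more later assessments (12 weeks, and the follow-up 6 months after the intervention).

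**Step 2. What is listed.** Every questionnaire, interview and cognitive task was read for a psychotic-symptom score.

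| Protocol list | Entries | Content | Psychotic-symptom score? |
|---|---|---|---|
| Clinical | 1 | Diagnostic interview for screening and comorbidity | No symptom score described, no follow-up administration stated |
| Screening | 1 | Physical activity readiness | No |
| Cannabis Use | 4 | Use, dependence, withdrawal, craving | No |
| Other Drug Use | 2 | Alcohol, nicotine | No |
| Psychopathology | 2 | Depression, anxiety | No |
| Wellbeing and Quality of Life | 5 | Quality of life, sleep, resilience, apathy, well-being | No |
| Weekly survey | 9 | Cannabis use, adverse events, "Patient Health Questionnaire (9-item", state anxiety, well-being, dependence, withdrawal, craving, mood sliders | No |
| Cognitive and figural memory tasks | 3 | Verbal and visual learning and memory | No |

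Entries checked: 1 + 1 + 4 + 2 + 2 + 5 + 9 + 3 = 27. Entries giving a repeated psychotic-symptom score: 0.

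**Step 3. Could the weekly survey stand in?** Its mood sliders cover mood, satisfaction, craving and energy, and nothing presents the Patient Health Questionnaire as a measure of psychosis. Table 1 also places the weekly questionnaires in the 12-week training column only, so they would not cover the 6-month follow-up. Adverse-event reporting is not a symptom scale.

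**Step 4. Coverage.**
- Domains in the psychopathology heading: 3. With an instrument: 2 (depressive symptoms, anxiety). Without: 3 − 2 = 1 (psychotic symptoms).
- Psychopathology components in Hypothesis 2a: 2. With an instrument: 1 (depressive symptoms). Without: 2 − 1 = 1 (psychotic symptoms).

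**Step 5. Consequence for the analysis.** With no baseline and no follow-up score, the group-by-time comparison for psychotic symptoms cannot be fitted. REML handling of missing values does not help, because the variable is absent for every participant at every visit. The mediation test in 2b uses the same outcome and fails for the same component. The primary model uses hippocampal integrity and does not depend on this variable.

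**The case against.** The best counter-argument is the diagnostic interview. It is listed under Outcome Measures, it assesses comorbidity as well as eligibility, and the telephone screen is described separately. A reader might infer that nothing in the protocol touches psychosis at all; the documents do not support that, because a psychiatric interview is given. What stands is narrower. No symptom score and no later administration are described for the interview, and Table 1 shows only questionnaires and cognitive activities at the 6-month follow-up. It cannot supply the change score that the analysis requires.

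A second objection is that the analysis section never names psychotic symptoms; it speaks of mental health in general, and depression and anxiety measures remain. That is fair as to the size of the gap, since the domain as a whole is still measured. It does not remove the mismatch with Hypothesis 2a, which names the component explicitly.

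A reader might also infer that social and occupational functioning is unmeasured. The documents do not support this. Hypothesis 2a places functioning within general well-being, the matching questionnaire section lists five instruments, and the choice of endpoint among them can properly sit in the statistical analysis plan.

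Nor does the exclusion of "Lifetime history of bipolar disorder, obsessive-compulsive disorder, post-traumatic stress disorder, psychosis or autism spectrum disorder" show that a psychosis scale would mostly read zero in this sample. Excluding a diagnosis says nothing definite about subclinical symptom scores, and the protocol gives no figure.

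**Conclusion.** The point holds in a limited form. One of the two psychopathology components of Hypothesis 2a has no instrument giving a score at baseline and follow-up, so it cannot be tested as change from baseline, and neither can its part of Hypothesis 2b. The hypothesis and the assessment list contradict each other and should be reconciled.

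The primary outcome, the depression component and the other secondary domains are unaffected. A reader might take this as a flaw that must be cured before the trial can be valid; that goes too far for one component of a secondary hypothesis which rewording alone can close. It is a correction that should be made.

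The conclusion assumes that the protocol's instrument lists are complete and that the interview is used only as described. Nothing around the psychopathology heading suggests removed text. The protocol does not state how many participants have been enrolled, so any loss of baseline data is conditional on that.

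**What to change.** Choose one of two changes.

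1. **Measure it.** Add one short self-report scale of psychotic-like experiences to the existing questionnaire battery at baseline, 12 weeks and the 6-month follow-up, and name it under the psychopathology heading. Table 1 already has questionnaires at all three assessments, so no new visit is needed. Cost: a few minutes per participant per visit and a protocol amendment.
2. **Remove it.** If baseline collection is no longer possible, delete psychotic symptoms from Hypothesis 2a and from the questionnaire heading, so that the stated hypothesis matches what is collected. Hypothesis 2b then follows without further change. Cost: a wording amendment, and the loss of this component as a pre-specified outcome.

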#### Wellbeing and Quality of Life

- Quality of Life and Satisfaction Questionnaire – Short Form (16-item)
- Pittsburgh Sleep Quality Index (24-item)
- Connor Davidson Resilience Scale (25-item)
- Apathy Evaluation Scale – Self Report (18-item)
- Warwick Edinburgh Mental Wellbeing Scale (14-item)

### *Weekly Qualtrics Questionnaire via Smart Phone*

Participants will be sent the Qualtrics link to their email and will be asked to complete the survey within 24 hours.

- Timeline Follow Back Procedure to measure weekly cannabis use
- Adverse Events
- Patient Health Questionnaire (9-item)
- State Anxiety Inventory – Short Form (6-item)
- Warwick Edinburgh Mental Wellbeing Scale – Short Form (7-item)
- Severity of Dependence Scale (5-item)
- Marijuana Withdrawal Checklist – Short Version (15-item)
- Penn Craving Scale (5-item)
- Visual Analogue Mood Scale: 100-point sliding scale indicating how the intensity of the following feelings over the last week:
  - Mood: happy – sad
  - Satisfaction: content – discontent
  - Cannabis craving: no craving – high craving, never – always
  - Energy: energized – lethargic

#### *Weekly Call*

- Identify and workshop barriers to engaging in EXE
- Check-in that EXE and weekly questionnaire has been completed
- Plan for week ahead (offer training with researcher, goal setting etc.)

#### *Cognitive*

Rey Auditory Verbal Learning Test (RAVLT): The RAVLT is a hand-administered task that evaluates a wide diversity of functions: short-term auditory-verbal memory, rate of learning, learning strategies, retroactive, and proactive interference, presence of confabulation of confusion in memory processes, retention of information, and differences between learning and retrieval. Participants are given a list of 15 unrelated words repeated over five different trials and are asked to repeat. Another list of 15 unrelated words are given and the client must again repeat the original list of 15 words and then again after 30 minutes.

Paired Associates Learning (PAL) Task: The computer-administered PAL task will be used to measure visual memory. Boxes are displayed on the screen and are “opened” in a randomised order. One or more of them will contain a pattern. The patterns are then displayed in the middle of the screen, one at a time and the participant must select the box in which the pattern was originally located. If the participant makes an error, the boxes are opened in sequence again to remind the participant of the locations of the patterns.

#### *Cardiopulmonary exercise testing (CPET)*

All participants will undergo two cardiopulmonary exercise testing (CPET) sessions to obtain a VO2 peak, heart rate peak, ventilation rates and respiratory exchange ratios. The assessment itself will take approximately 10 minutes, however participants will be asked to allow 45 minutes to accommodate pre-test and post-test procedures. They will perform a graded

exercise test to volitional exhaustion on a treadmill. The starting metabolic intensity (METS) will be 4.6, increasing 2.7 METS every 3 mins (i.e. starting speed at 3kph, increasing 2kph every 3 mins; and incline is fixed at 9% gradient). End-test criteria is determined by participant's subjective indication to stop the test, or for any safety reason determined by the supervising Exercise Physiologist. During the CPET, inhaled and expired gas will be continually analysed every 10 secs using an on-line breath-by-breath system (ADInstruments). Ratings of perceived exertion (Borg Scale) will be recorded every 60 secs. Participants will wear a face mask during the CPET to allow ADInstruments' hardware and software to capture inhaled and expired gases. All CPET sessions will be conducted at BrainPark.

#### Heart Rate

Each participant will wear a Polar heart rate strap during exercise sessions, and Polar software will be used for data collection. The Polar hardware and software allows real time monitoring and post-session raw data analysis via an online portal. Heart rate monitoring aids the supervising exercise physiologists in making necessary modifications to participant exercise prescription, and verbal feedback, to ensure heart rate responses are reasonably achieving protocol targets. At the completion of data collection the research team will use the final data set to analyse volumes of time spent above key heart rate thresholds - allowing between-, and within-, group comparisons.

#### Engagement

The research team will document participant attendance for each exercise session to quantify individual, and group level, engagement rates.

#### MRI

Participants will complete a 1hr MRI session on a 3T Siemens Skyra located on-site at Monash Biomedical Imaging building. Scanning will involve T1-weighted, and T2-weighted image sequence for high-resolution images; diffusion-weighted sequence (DTI) to probe the microstructural content of brain white matter. This sequence will consist of 60-diffusion-encoding gradients ( $b=3000 \text{ s/mm}^2$ ;  $2.5 \text{ mm}^3$  voxel size).

The scanning sequence is as follows:

1. Structural scan 1: T1-weighted (5.5min)
2. Structural scan 2: T2-weighted (5min)
3. Left Hippocampal MRS (12min)
4. Resting state fMRI (8min)
5. DTI (12 min)
6. fMRI with figural memory cognitive task (7min)

#### Figural memory task

The figural memory task (Jamadar et al., 2013) is a visual encoding and recognition task designed to minimize verbal encoding of picture stimuli. The task stimuli (20 targets and 20 distractors) consisted of black line drawings presented against a white background.

Participants perform an encoding phase and a recognition phase during fMRI scanning. During the encoding phase 20 target stimuli are presented (duration 3 s, interstimulus interval (ISI) 4 s), which participants were instructed to memorise. Participants press a response box button following each stimulus presentation to confirm that they saw the stimulus. The recognition phase follows the encoding phase after a 12-min delay (with no other cognitive task presented during the delay). During the recognition phase, 20 target and 20 distractor stimuli are presented in a fixed pseudo-random order, each for 3 s with an ISI of 4 s. Participants held the button box in their non-dominant hand and pressed a button with the index finger of their dominant hand. The button on the right ("old") or button on the left ("new") fingers to indicate whether they had previously seen each stimulus, and accuracy was emphasized over speed.

### *Biological Assays*

#### Urine

Urine samples will be collected at baseline and end of intervention to measure the presence of THC-COOH, a secondary metabolite of THC present in cannabis. Prior to collection, participants will be asked to wash their hands to eliminate any possible adulterating or contaminating substances from under participant's fingernails. Participants will be provided with a clean, unused urine specimen collection container and requested to fill the container at least half full (a minimum of 30 mL's) with their urine. Participants will be provided with a private toilet stall for the procedure. Urine specimens will be stored in a secure deep-freezer until the specimen is ready to be shipped to a toxicology laboratory for analysis.

#### Hair

Hair samples will be collected at baseline and at the end of intervention assessments to measure the presence of THC and THC-COOH using laboratory-recommended procedures, whereby collection will be performed within a secure contamination free room with access restrictions in place. The collector will wear gloves and use clean tools to avoid any risk of interindividual contamination. The posterior vertex region of the head will be the preferred sampling site as this region is associated with the smallest variation in growth rate. A lock of hair that is approximately 200mg will be tied, cut as close to the skin as possible and collected. The root end of scalp hairs will be aligned and clearly identified. The sample will be firmly secured, e.g. with an aluminum foil, to maintain integrity and avoid contamination. Hair samples will be stored in a dry, dark environment at room temperature until the specimen is ready to be shipped to a toxicology laboratory for analysis.

#### Saliva

Participants will be asked to provide a saliva sample at baseline to measure candidate genes that may influence individuals' response to the EXE intervention. Samples will be collected utilising Oragene saliva collection kits. Oragene tubes will be labeled prior to sample collection with participant ID and date. The participant will be asked not to eat, drink (including water), smoke or chew gum for 30 minutes before giving the saliva sample. While Wearing Gloves the researcher will hand the assembled oragene tube to the participant and

ask them to spit into the funnel of the tube until the amount of liquid (excluding bubbles) reaches the fill line this should take approximately five minutes. The researcher will then ask the participant to close the funnel lid and then bend the lid over the catchment area until it snaps closed and the liquid is released into the collection tube. The tube will be wiped down with ethanol to remove traces of saliva from the tube. The samples will be stored in the MBI biohazard room with restricted access. Saliva samples will be kept until all samples are collected from the cohort prior to being sent for analysis. The saliva samples can be stored for 5 years at room temperature. Saliva samples will be sent to the Australian Genome Research Facility where they will undergo a DNA extraction and replication process before SNP genotyping using Agena Bioscience MassARRAY mass spectrometry. A candidate genes approach will be employed to assess individual differences in the response to the intervention. Candidate genes will be selected based on priori knowledge regarding genes which are known to underpin the neurobiological processes which may influence response to the intervention.

### **Assessment of Adverse Effects**

Participants will receive weekly telephone calls to monitor for adverse events associated with physical exercise and general study protocol. Adverse events will also be monitored in session by the exercise physiologists.

### **Payment**

Participants will receive \$15 compensation for each exercise training sessions and \$50 compensation for each of the three clinical assessments attended (baseline, 12-weekss and 6-months). These monies will be provided to compensate participants for the substantial time and effort involved in attending 12-weeks of frequent exercise and assessment sessions and contribute to parking / transport costs.

### **Recruitment**

Large-scale community advertising via print media will be used to advertise the study. Flyers will be placed throughout local health centres, medical centres, community centres, community notice boards, university campuses, on the internet and social media. The study will also be advertised via Directline, a 24/7 alcohol and drug helpline run by Turning Point.

## **Statistical analysis plan**

Primary Outcome: Hippocampal integrity will be analysed using a linear regression model with a clustered sandwich estimator to account for the repeated measures and will include the main effects of intervention group (EXE [+/-] and time [0-, 3-months]), as well as their interaction (see Fig. 5), whilst adjusting for potential confounders (to be specified in the SAP). For Hypothesis 1, greater efficacy of EXE+ will be confirmed if there is significantly greater change in hippocampal integrity at 3-months relative to baseline in the EXE+ compared to EXE- group.

Secondary Outcomes: Hypothesis 2 will be tested using linear mixed models with restricted maximum likelihood estimation (REML) for handling missing values. Particularly, the models will compare changes in outcomes from 'baseline to 3- months' and 'baseline to 6- months', with main effects of intervention group (EXE [+/-]) and time plus their interaction. The benefits of EXE+ will be supported if there is significantly greater change in the behavioural and functional outcomes measured at 3-months, and/or at 6-months (relative to baseline), in the EXE+ compared to EXE- group. Hypothesis 2b will test whether the changes in behavioural (cannabis use) and functional (cognitive, mental health, general well-being) outcomes (i.e., Hypothesis 2a) are mediated by the changes in hippocampal integrity (i.e., Hypothesis 1). We will test this prediction using longitudinal mediation models [43].

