## Method

### Participants

One hundred and fifty cannabis users (aged 20 – 55 years) from the community and referred from Turning Point, a national service provider that engages with thousands of cannabis users each year, whom are seeking to reduce their cannabis use but are not currently enrolled in treatment, will be recruited into the study.

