**Procedure**

The study will employ a single-blind, active-controlled, parallel group randomised design. Participants will be randomised to engage in a 12-weeks program of one of the following two physical training conditions:

- a. EXE+ condition: 12-weeks of HIIT
- b. EXE- condition: 12-weeks of strength training

Following recruitment and written informed consent, participants will be randomly allocated to the study groups in a 1:1 ratio using permuted blocks of random size generated by a statistician not involved in the study. Group allocation will be stratified to balance cannabis dependence severity (according to the severity of dependence scale (SDS)) and sex. We will

also employ post-stratification assessments of key variables at the analysis stage (including age, baseline fitness, and nicotine use). Treatment allocation concealment will be achieved by using a password protected computer program, implemented by an independent member of the Monash University administration team who will inform the research team about the randomisation outcome. Following randomisation, participants will be informed about the assessment protocols, and the EXE program.

Outcome measures will assess psychological (questionnaires), biological (MRI, MRS, urine assays, hair and saliva assays), cognitive (hippocampal function), cannabis use (questionnaires) levels of fitness (VO2 test), and physical activity (heart-rate physical activity via Garmin device). Primary assessments will be made at baseline, end of 12-week and 6-month post-intervention follow up review. Brief assessment of psychological wellbeing and cannabis use will be made weekly via the Qualtrics smartphone platform. The intervention and assessment schedule is depicted below in Table 1.

**Table 1.** Participant Timeline of Testing Procedures

| Pre-training                   | 12-week training                        | Post-training          | 6-month follow up    |
|--------------------------------|-----------------------------------------|------------------------|----------------------|
| MRI brain scan                 | 3x weekly exercise                      | MRI brain scan         | Questionnaires       |
| Questionnaires                 | 1x weekly phone call and questionnaires | Questionnaires         | Cognitive activities |
| Cognitive activities           |                                         | Cognitive activities   |                      |

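### The secondary mixed models give each randomised arm its own baseline mean and test change from baseline, which is valid but less efficient than a common-baseline or baseline-adjusted model

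*Protocol*

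**What the plan says.** In the Protocol, section Statistical analysis plan, the secondary paragraph fixes three things.

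- **Method:** "Hypothesis 2 will be tested using linear mixed models with restricted maximum likelihood estimation (REML) for handling missing values".
- **Contrast:** "the models will compare changes in outcomes from 'baseline to 3- months' and 'baseline to 6- months" are the two comparisons.
- **Terms and criterion:** the model is written "with main effects of intervention group (EXE [+/-]) and time plus their interaction. The benefits of EXE+ will be supported if there is significantly greater change". Success for EXE+ may come at either follow-up.

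The paragraph names no covariates and excludes none. The primary paragraph of the same section uses the same three terms, but adds that the model is fitted "whilst adjusting for potential confounders (to be specified in the SAP").

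Under Procedure, allocation is randomised 1:1, and "Group allocation will be stratified to balance cannabis dependence severity (according to the severity of dependence scale (SDS)) and sex". The same section says the team will "also employ post-stratification assessments of key variables at the analysis stage (including age, baseline fitness, and nicotine use"). Table 1 schedules questionnaires and cognitive tasks before training, so baseline values of these outcomes will be available. Participants gives the size: "One hundred and fifty cannabis users (aged 20 – 55 years").

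**The concern.** Baseline enters these models as an outcome, and the group main effect is the difference between arms at baseline. Random allocation makes that difference zero in expectation, so the model estimates a quantity already known from the design. The group-by-time contrast then subtracts the observed baseline difference in full, whereas the best use of baseline subtracts only the part that predicts follow-up.

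The cost is precision. These models carry the clinical questions of the trial: cannabis use, psychopathology, learning and memory, and functioning. The sample is set at 150, so a wider standard error raises the chance of missing a real effect, and nothing is gained in return.

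**Working it through.** The protocol states no power, effect size, SD, correlation or significance level, so there is no figure to reproduce.

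**Inputs from the Protocol:** 150 participants allocated 1:1, so 75 per arm; model terms group, time and their interaction; contrast is change from baseline.

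**Assumptions:** two-sided 5% level; SD of 1 at baseline and follow-up; correlation rho from 0.3 to 0.9.

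**Step 1: variances.** Per person:

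- Change score: 1 + 1 − 2·rho = 2(1 − rho).
- Follow-up given baseline (the constrained or adjusted analysis): 1 − rho².
- Ratio: 2(1 − rho) / [(1 − rho)(1 + rho)] = 2/(1 + rho).

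With unequal SDs s0 and s1, the change-score variance exceeds the adjusted variance by (s0 − rho·s1)². This is never negative, so in large samples the change contrast is never the more precise one.

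**Step 2: power, with the written model set at 80%.** The standardised effect under the written model is 1.960 + 0.842 = 2.802. Under the alternative it is 2.802·√(2/(1+rho)), and power = Φ(that − 1.960). At rho 0.5: 2.802 × 1.155 = 3.235, and Φ(1.275) = 0.899.

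| rho | Variance ratio | Power, written | Power, constrained or adjusted |
|---|---|---|---|
| 0.3 | 1.54 | 80% | 93.5% |
| 0.5 | 1.33 | 80% | 89.9% |
| 0.7 | 1.18 | 80% | 86.0% |
| 0.8 | 1.11 | 80% | 84.0% |
| 0.9 | 1.05 | 80% | 82.0% |

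**Step 3: power at a fixed effect of 0.4 SD, 75 per arm.** At rho 0.5 the written model has SE √(2/75) = 0.163, so 0.4/0.163 = 2.449 and power is Φ(0.489) = 0.688. The adjusted SE is 0.163 × √0.75 = 0.141, which gives Φ(0.868) = 0.807.

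| rho | Written | Constrained or adjusted |
|---|---|---|
| 0.3 | 54% | 73% |
| 0.5 | 69% | 81% |
| 0.7 | 89% | 93% |
| 0.8 | 97% | 98% |
| 0.9 | about 100% | about 100% |

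The effect detectable with 80% power is 0.46 SD against 0.40 SD at rho 0.5, and 0.35 SD against 0.33 SD at rho 0.7.

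**Step 4: check in fitted models.** Three-visit trials of 150 were simulated and fitted by REML with a random intercept, 12 per scenario. SDS and sex were assumed to explain 20% of the variance. Twelve trials are too few to judge empirical spread, so only average model SEs at the first follow-up are shown.

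| Scenario | Written | Written + SDS, sex | Constrained | Constrained + SDS, sex |
|---|---|---|---|---|
| rho 0.5, complete | 0.163 | 0.163 | 0.142 | 0.136 |
| rho 0.5, 25% dropout | 0.1715 | 0.1705 | 0.151 | 0.144 |
| rho 0.7, complete | 0.126 | 0.126 | 0.117 | 0.114 |
| rho 0.7, 25% dropout | 0.1341 | 0.1336 | 0.125 | 0.122 |

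With complete data the written estimate equalled the raw difference in mean change to within 4e-15, and adding SDS and sex as main effects left it unchanged. With 25% dropout it differed from the raw difference by up to 0.05 SD at rho 0.5, but the precision gap remained.

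**The case against.** **The model is conventional and answers the question asked.** This stands. Randomisation makes the difference in change unbiased, and chance baseline imbalance adds variance, not bias. A reader might infer that the secondary results would be biased; the documents do not support that.

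**Covariates belong to the SAP, which is not at hand.** This stands for the covariate list. A reader might infer that the models contain only three terms and that SDS and sex are left out. The paragraph is silent on covariates, and the analysis-stage list under Procedure is open-ended and tied to no particular outcome. The objection does not reach the main point, because the group main effect and the change contrast are in the protocol text, and covariates added as main effects do not recover the loss (Step 4).

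**The strata do not drive the loss.** This also stands. Main effects of SDS and sex cancel from within-person change. With complete data their omission costs the written model nothing, and with 25% dropout under 1% of the SE. They help only once baseline is constrained, and the size of that help rests on the assumed 20% of variance.

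**The primary model has the same structure.** True: it too has a group main effect and an interaction, so this is not a gap peculiar to the secondary outcomes.

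**The loss may be small.** At rho of 0.7 or above it is modest, and at 0.9 it nearly vanishes. It also shrinks if baseline spread is narrower than follow-up spread, which is plausible for cannabis frequency given the entry requirement of at least 3 days a week over years. But Hypothesis 2a covers several different outcomes over months, so one high correlation cannot be presumed for all of them.

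**Conclusion.** The point holds as one of efficiency. The secondary models as written are valid and unbiased, but for equal SDs they are less precise than a common-baseline or baseline-adjusted model at every rho below 1. Against an 80% anchor the gain in power runs from about 13.5 points at rho 0.3 to 4 at rho 0.8. At a fixed 0.4 SD it is about 18 points at rho 0.3, 12 at 0.5, 4 at 0.7 and 1 at 0.8. It is therefore material at rho of 0.5 or below and small at 0.7 or above.

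These figures rest on assumed correlations, equal SDs, 75 per arm with complete data and a two-sided 5% level; none of the correlations or SDs can be taken from the protocol. A reader might infer that every secondary contrast will be a raw difference in change. That is exact only with complete data, and the plan chooses REML because it expects missing values. This is a recommended improvement to secondary analyses, not an error that invalidates them.

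**What to change.** In the secondary paragraph of the Statistical analysis plan, replace the group, time and interaction terms with one of the following.

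- A REML mixed model with visit and group × post-baseline visit, no group main effect (baseline means constrained equal across arms) and an unstructured covariance over the three visits.
- A model of the two follow-up values with visit, group × visit and baseline value × visit.

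In either case, report the group contrast at each follow-up visit. As a minor addition, include SDS stratum and sex as used in the randomisation.

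Both options assume that baseline measures cannot be affected by allocation. Procedure does not state outright that baseline assessment is completed before participants learn their arm, so the same edit should confirm this.

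**Cost:** one or two sentences and no new data. With three visits the constrained model has five fixed effects (intercept, two visit, two group-by-visit) against six as written. An unstructured covariance has six parameters, against two for a random intercept. If SDS enters as two levels, the strata add two parameters as main effects, or six if they also vary by visit. That is a few nuisance parameters at N = 150.
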